## Abstract

**Background:**

Intrahepatic cholestasis of pregnancy (ICP) is the most common liver disorder unique to pregnancy, associated with elevated maternal bile acid concentrations and adverse perinatal outcomes.

**Methods:**

This is a prospective cohort study conducted in a level III neonatal unit in Bucharest, Romania. Neonates born to mothers with ICP (serum bile acids ≥10 μmol/L within seven days before delivery) will be enrolled alongside gestational age, sex and birthweight-matched controls. Serum samples will be collected at 24 h, 48–72 h and on day 7 of life. Quantitative ELISA kits will be used to assess serum biomarkers associated with surfactant dysfunction and lung injury. Perinatal and clinical outcomes will be recorded systematically.

**Results:**

The primary aims are to compare the incidence of respiratory distress syndrome (RDS), the need for surfactant administration and serum biomarker profiles between ICP-exposed and unexposed neonates. Secondary aims include evaluating respiratory support requirements, neonatal morbidity and mortality across groups.

**Conclusions:**

We expect that neonates exposed to maternal cholestasis will have a higher incidence of RDS, increased surfactant need, and biomarker alterations consistent with pulmonary compromise. This study may improve understanding of bile acid-related lung injury and inform early risk stratification strategies in affected newborns. (NCT06679972).

## Introduction

1

Intrahepatic cholestasis of pregnancy (ICP) is the most common hepatobiliary disorder unique to pregnancy, with a reported incidence of 2.9%, depending on geographic and ethnic factors (1). ICP is characterized by maternal pruritus and elevated serum bile acid concentrations, typically emerging during the third trimester. Although maternal symptoms resolve postpartum, ICP is associated with significant perinatal complications, including spontaneous preterm birth, meconium-stained amniotic fluid, fetal distress, and an increased risk of intrauterine demise (2, 3).

Beyond its established association with stillbirth and prematurity, emerging evidence has highlighted a potential link between ICP and neonatal respiratory morbidity. Several studies have demonstrated an increased incidence of RDS among neonates born to mothers with intrahepatic cholestasis of pregnancy, independent of gestational age at delivery (4, 5). Experimental data suggest that elevated fetal bile acid levels may interfere with surfactant synthesis or function, disrupt alveolar integrity and contribute to early pulmonary injury (6). However, the biological pathways underlying this relationship remain poorly understood.

Serum biomarkers of surfactant dysfunction and lung injury have been well characterized in the context of neonatal respiratory complications such as RDS and bronchopulmonary dysplasia (7). Nevertheless, no study to date has systematically evaluated these biomarkers in neonates exposed to maternal cholestasis. Consequently, it remains unknown whether intrauterine exposure to elevated bile acid levels induces biochemical evidence of surfactant impairment or pulmonary injury detectable at birth. Quantifying the extent of lung compromise in this population may not only provide insights into disease pathophysiology, but also support early risk assessment and targeted interventions in the neonatal period.

The CHOLE-RESP study has been designed to address these gaps by prospectively evaluating the incidence of RDS and the need for surfactant therapy in neonates born to mothers with ICP compared to matched controls. In addition, this study seeks to determine whether neonates exposed to intrahepatic cholestasis of pregnancy exhibit distinct serum biomarker profiles consistent with lung injury and surfactant impairment, thereby elucidating a potential link between maternal cholestasis and early neonatal respiratory dysfunction.

## Methods and analysis

2

### Study design

2.1

This is a single-center, prospective cohort study conducted in the Neonatology Department of the “[name]. Panait Sîrbu” Clinical Hospital of Obstetrics and Gynecology in Bucharest, Romania. The study initiated enrolment on October 1st 2024 and is expected to complete recruitment by December 31st 2027, after which follow-up and data analysis will be conducted.

Eligible study participants (neonates born at term or preterm age), enrolled by invitation, will be recruited following the provision of written informed consent by the legal guardian (the mother). The rights and welfare of all participants will be protected in accordance with the principles outlined in the Declaration of Helsinki.

A SPIRIT schedule and overview of the study design can be found in Figures 1, 2.

**Figure 1 F1:**
[figure not shown]
SPIRIT schedule of enrolment, interventions, and assessments. Visual representation of the SPIRIT timeline outlining timepoints for eligibility screening, informed consent, allocation, interventions, and outcome assessments. Samples are scheduled at 24 h, 48–72 h and on day 7 of life (if hospitalized), with follow-up data collected until 3 years after initial enrolment. RDS, respiratory distress syndrome; NICU, neonatal intensive care unit.

**Figure 2 F2:**
[figure not shown]
CHOLE-RESP study design timeline. Simplified schematic of the CHOLE-RESP study protocol from ethics approval through sample collection and follow-up.

This protocol has been developed following the Standard Protocol Items: Recommendations for Interventional Trials checklist (see Supplementary Table 1) (8).

### Study objectives

2.2

The primary objectives of this study are to evaluate the incidence of RDS, to assess the need for exogenous surfactant administration and to compare serum biomarker profiles indicative of surfactant dysfunction and pulmonary injury between ICP-exposed and unexposed neonates.

For clarity, these are defined as follows:

RDS is defined as a clinical diagnosis made within the first 72 h of life, based on signs of respiratory compromise (tachypnea, grunting, nasal flaring, chest retractions), supportive radiographic findings and a need for supplemental oxygen or respiratory support.

Surfactant administration refers to any administration of exogenous surfactant therapy within the first 72 h of life, regardless of dosing or mode of delivery.

Biomarker profile includes the quantitative assessment of serum biomarkers related to pulmonary injury and surfactant deficiency, measured at 24 h, 48–72 h and on day 7 of life when available.

Secondary objectives include evaluating respiratory morbidity, such as the need for mechanical ventilation and non-invasive respiratory support, as well as the occurrence of serious respiratory complications including pneumothorax, pulmonary hemorrhage and persistent pulmonary hypertension. Additional secondary objectives include assessing neonatal intensive care unit (NICU) admission, length of hospitalization and in-hospital neonatal mortality.

### Sample size calculation

2.3

An *a priori* power analysis was performed using JASP (version 0.19.2) to estimate the required sample size for detecting a between-group difference in biomarker levels with adequate statistical power. Assuming a one-sided independent samples *t*-test, a medium effect size (Cohen's |*δ*| = 0.5), a Type I error rate (*α*) of 0.05 and a target power (1−*β*) of 0.95, the analysis indicated that a minimum of 66 participants in the ICP-exposed group and 132 in the unexposed group would be required to achieve an actual power of 0.952.

These parameters were selected to align with the study's directional hypothesis that intrahepatic cholestasis of pregnancy is associated with poorer respiratory outcomes and higher biomarker levels. A 2:1 unexposed-to-exposed ratio was adopted to address the lower expected incidence of neonates with maternal ICP, providing greater statistical precision while also enhancing generalizability and minimizing bias, without placing disproportionate demands on recruitment. Also, the higher power threshold of 0.95 was chosen to ensure adequate sensitivity for detecting clinically meaningful biomarker differences, which represent a novel co-primary objective and a central component of the study's design.

This configuration provides robust power to detect moderate effect sizes over 0.5 with high reliability, acknowledging that smaller effects (|*δ*| ≤ 0.25) are associated with a substantially reduced probability of detection. Accordingly, a minimum of 198 neonates will be enrolled to meet the sample size requirements established by the power analysis.

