### Statistical analysis

2.8

Statistical analysis will be performed using JASP 0.19.2. Frequency analysis will be performed using contingency tables. Group differences in the incidence of RDS and the need for surfactant therapy will be assessed using the chi-squared test or Fisher's exact test, where expected cell counts are less than five. Differences in mortality will be evaluated descriptively using odds ratios (ORs), and if event frequency permits, time-to-event analysis may be considered. In addition, time-to-event outcomes such as time to first surfactant dose, time to intubation and time to second surfactant administration will be analyzed using Kaplan–Meier curves and compared using the log-rank test, with Cox regression models applied where appropriate.

Serum biomarker levels indicative of lung injury will be compared between groups at each time point using the Student's *t*-test for normally distributed data or the Mann–Whitney *U* test when normality is not assumed. To assess longitudinal trends in biomarker levels, repeated-measures ANOVA or linear mixed-effects models will be employed, depending on data distribution and completeness. For non-parametric repeated data, the Friedman test may be used. Normality and homogeneity of variances will be tested using the Shapiro–Wilk and Brown-Forsythe tests, respectively. A significance level of 0.05 will be used for all analyses. For normally distributed biomarker data, standardized mean differences between groups will be reported as Cohen's d and Glass's delta. To account for potential residual confounding, gestational age at birth, matched during enrollment, will additionally be included as a covariate in relevant statistical models and stratified analyses may be performed to explore outcome differences across gestational age subgroups.

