Nevertheless, certain limitations are anticipated. As a single-center study, generalizability may be limited, though the use of carefully matched controls mitigates this to some extent. Practical constraints may occasionally lead to delays in sample centrifugation, in which case samples will be stored at 2–5 °C in a dedicated medical-grade refrigerator. Sample hemolysis or insufficient serum volume may affect the ability to test all biomarkers, however these deviations will be documented transparently and addressed in the final analysis. Although early neonatal death is expected to be rare, it may act as a competing risk for outcomes such as RDS. Therefore, all mortality events and their timing will be recorded and considered in the interpretation of respiratory outcomes.

Ethical considerations have been fully integrated into the study design. Informed consent is obtained only after obstetric teams confirm an imminent delivery and before administration of anesthesia. Mothers are given time and autonomy to ask questions and are clearly informed of their right to decline or withdraw participation, without any impact on neonatal care. Blood samples are collected exclusively during procedures already indicated for clinical care, otherwise, if no clinical indication exists or the neonate's condition prohibits collection during a designated window, the sample is skipped and the reason will be included in the study's final reporting.

The CHOLE-RESP study has the potential to significantly advance the field by providing the first structured clinical and biochemical assessment of neonatal respiratory outcomes following ICP exposure. If the study confirms a measurable link between bile acid exposure and pulmonary injury, this could support the development of risk-based screening tools and tailored respiratory management strategies. Moreover, growing evidence from metabolomic and proteomic research suggests that intrahepatic cholestasis of pregnancy is associated with complex molecular signatures extending beyond bile acid concentrations alone (15, 16). Within this framework, the present study lays the groundwork for future multicenter validation efforts, broader biomarker profiling and the integration of hypothesis-generating omics approaches aimed at refining risk stratification and improving outcomes in this understudied neonatal population.

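### The stated power of 0.952 holds only if all 198 enrolled neonates yield an analysable serum value under the one-sided test; the sampling rules allow for missing samples and the calculation does not

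*Protocol article*

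**What the plan says.** Section 2.3 (Sample size calculation) powers the study on a difference in biomarker levels. The inputs are given openly: "Assuming a one-sided independent samples" *t*-test, "a Type I error rate (*α*) of 0.05", a standardised difference of 0.5 and a power target of 0.95. The one-sided choice is explained: "These parameters were selected to align with the study's directional hypothesis". The result is 66 exposed and 132 unexposed neonates, which "would be required to achieve an actual power of 0.952". The section then turns this into a recruitment figure: "a minimum of 198 neonates will be enrolled to meet the sample size requirements established by the power analysis". It adds no allowance for missing or unusable samples.

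Other sections determine how many of those neonates will have a biomarker value:

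- Section 2.5 (Sample collection) plans a first sample within 24 h. The 48–72 h sample depends on clinical stability and on a reason for further routine tests. A day 7 sample may be taken in infants who stay longer.
- The Discussion restricts blood collection to procedures already indicated for care. If there is none, or the infant's condition does not permit it, the sample is skipped and the reason reported. It also warns: "Sample hemolysis or insufficient serum volume may affect the ability to test all biomarkers".
- Section 4 (Ethics and dissemination) repeats that samples come only from routine draws and foresees haemolysed or insufficient serum.

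Section 2.8 (Statistical analysis) compares biomarkers between groups at each time point by *t*-test or Mann–Whitney test. On the error level it says: "A significance level of 0.05 will be used for all analyses". It does not say whether the biomarker test is one- or two-sided.

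**The concern.** A power calculation for a laboratory measurement counts measurements, not infants enrolled. Section 2.3 treats the two as equal, while three other parts of the same article describe ways in which an enrolled infant may have no usable measurement. The study takes both term and preterm neonates, and a well term infant may have few indicated blood draws, so the later time points are the most exposed.

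The figure matters because the article relies on it. Section 2.3 defends 0.95, rather than a lower conventional target, as a deliberate choice to secure sensitivity for a novel co-primary objective, and describes the power as robust. A reader facing a non-significant comparison at 48–72 h or day 7 could take 0.95 as the sensitivity of that comparison, when the number of infants sampled at that time may be well below 198.

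Sidedness is a smaller, related matter. The power figure depends on a one-sided test, and the section that specifies the test does not carry that choice forward.

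**Working it through.** **Inputs from section 2.3.** Standardised difference d = 0.5; α = 0.05, one-sided; n₁ = 66 exposed; n₂ = 132 unexposed; target power 0.95.

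**Formula.** Exact noncentral *t*:

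- degrees of freedom = n₁ + n₂ − 2
- noncentrality λ = d × √(n₁n₂ / (n₁ + n₂))
- one-sided power = P(T′ > t₀.₉₅), where T′ is noncentral *t* with parameter λ
- two-sided power uses t₀.₉₇₅ and adds the opposite tail, which is negligible here

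**Step 1: reproduce the stated figure.** λ = 0.5 × √(66 × 132 / 198) = 0.5 × √44 = 3.317. With 196 degrees of freedom the one-sided critical value is 1.653, and power is 0.9516. The stated 0.952 is confirmed.

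**Step 2: is there slack?** For 65/130, λ = 0.5 × √(65 × 130 / 195) = 3.291 and power is 0.949. So 66/132 is the smallest 1:2 design that reaches 0.95. Losing the values of one exposed infant and two controls already misses the target.

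**Step 3: power when samples are missing.** The documents give no loss rate. The fractions below are assumptions, applied equally to both groups. The two-sided column is conditional on that test being used.

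| Evaluable (assumed) | Exposed / unexposed | One-sided 0.05 (as in 2.3) | Two-sided 0.05 (if used) |
|---|---|---|---|
| 100% | 66 / 132 | 0.952 | 0.910 |
| 90% | 59.4 / 118.8 | 0.932 | 0.879 |
| 80% | 52.8 / 105.6 | 0.905 | 0.839 |
| 70% | 46.2 / 92.4 | 0.868 | 0.787 |
| 50% | 33 / 66 | 0.753 | 0.641 |

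Rounding the 80% row down to whole infants (52/105) gives 0.902 and 0.834, hence 0.90 and 0.83–0.84.

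**Step 4: unequal loss.** If all exposed infants are evaluable but only half the controls are (66/66, again assumed), one-sided power is 0.887.

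**Step 5: how much loss matters.** Under the protocol's own one-sided test, about 19% loss is needed before power falls to roughly 0.91. The two-sided test reaches 0.910 with no loss at all, and would need 79 + 158 = 237 complete samples to reach 0.95 (power 0.951).

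**The case against.** The strongest reply is that nothing has been miscalculated. The figure is right for its inputs, and every power statement holds only under its assumptions. That stands: this is not an arithmetic error.

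A reader might also infer that the test is really two-sided and that the true power is therefore 0.91. The documents do not support this. Section 2.3 declares a one-sided test and gives a directional reason, and the abstract's expectations point the same way. Section 2.8 is silent on sidedness, which is not a contradiction. Describing an objective as a comparison does not declare a two-sided hypothesis, and the chi-squared and log-rank tests serve other outcomes. The figure of 0.91 is conditional only.

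Some protection against missing samples exists. Section 2.2 defines the biomarker profile by what is available, section 4 defers a missed draw to the next scheduled test within the window, section 2.8 allows mixed models depending on completeness, the article commits to reporting skipped samples, and 198 is a minimum that may be exceeded. These points stand, and first-sample loss may prove small. But none of them changes the power statement, and no over-enrolment is planned. Reporting missing samples afterwards is not the same as allowing for them in the calculation.

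Finally, the protocol already concedes reduced power for effects of 0.25 or less. That concession concerns small effects and does not cover missing samples at the planned effect of 0.5.

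**Conclusion.** The concern holds in a limited form. The 0.952 is correct for a one-sided 0.05 *t*-test with an analysable value from each of 66 exposed and 132 unexposed neonates. The sampling rules do not promise that at any time point, and at 48–72 h and day 7 they make it unlikely. Because the design is the smallest that meets the target, even a small loss in both groups takes power below 0.95.

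The size of the shortfall is unknown, since no loss rate is given. Under the protocol's own test it is modest at 10% loss (0.93), clearer at 20–30% (0.90 to 0.87), and substantial at 50% (0.75). These figures assume d = 0.5, normally distributed data and equal loss in both groups.

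It should not be inferred that the study is underpowered in general or that recruitment must be increased. Power stays near 0.90 with one sample in five missing, and the shortfall is against the article's own 0.95. The missing statement of sidedness in section 2.8 is an item to reconcile, not a second error.

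**What to change.** 1. In section 2.3, state that 0.952 applies to 66 exposed and 132 unexposed neonates with an evaluable sample at the time point compared, under the one-sided 0.05 test.
2. In the same place, add the power of that test at assumed evaluable fractions: 0.93 at 90%, 0.90 at 80%, 0.87 at 70% and 0.75 at 50%. Label these as assumptions, and note that the 48–72 h and day 7 comparisons are likely to have lower power than the first.
3. In section 2.8, state that the biomarker comparison is one-sided at 0.05. If it will instead be run two-sided, restate the power as 0.91 with complete samples, 0.83–0.84 at 80% evaluable and 0.64 at 50%.

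The minimum of 198 can remain as an enrolment figure, and the other tests need not change. The work is a few sentences in two sections. The cost is that the stated power becomes less favourable.

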### Eligibility criteria

2.4

Participants will be enrolled into either the exposed or unexposed group based on predefined eligibility criteria. The exposed group will consist of neonates born to mothers with a recent diagnosis of intrahepatic cholestasis of pregnancy, defined by serum bile acid concentrations exceeding 10 µmol/L within seven days prior to delivery. Furthermore, written informed consent needs to be obtained at least one hour prior to birth. No minimum gestational age at delivery is imposed and eligible neonates must be either born at the study location or transferred to the unit from another neonatal facility within the first 24 h of life. Exclusion from this group will apply in instances where informed consent is not provided, where no serum bile acid measurement is available in the specified time frame or where measured bile acid levels are below 10 µmol/L.

The unexposed group will comprise neonates born at the same institution to mothers without a known history of hepatic disease prior to or during the index pregnancy. Controls will be matched according to gestational age at birth, birthweight and sex. Consistent with the ICP-exposed group, informed consent must be obtained a few hours before delivery. Maternal administration of ursodeoxycholic acid at any point during pregnancy, regardless of dosage or timing, will constitute an exclusion criterion for this group, as it may suggest subclinical hepatic dysfunction.

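### Exposed neonates may be transferred in within 24 h but controls must be inborn, so any outborn exposed neonates could inflate the ICP group's respiratory outcomes

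*Protocol article*

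**What the plan says.** Section 2.4 (Eligibility criteria) sets the entry rules group by group.

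- **Exposed group, place of birth:** "eligible neonates must be either born at the study location or transferred to the unit from another neonatal facility within the first" (the limit is 24 h).
- **Exposed group, consent:** "written informed consent needs to be obtained at least one hour prior to birth". Sections 3 and 4 add that consent follows the obstetric team's confirmation that delivery is near and precedes anesthesia.
- **Unexposed group, place of birth:** "The unexposed group will comprise neonates born at the same institution to mothers without a known history of hepatic disease". No transfer route is given.
- **Matching:** "Controls will be matched according to gestational age at birth, birthweight and sex".

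Section 2.2 counts both respiratory co-primary outcomes over a window that includes the transfer period: "RDS is defined as a clinical diagnosis made within the first 72 h of life", and surfactant use is "any administration of exogenous surfactant therapy within the first 72 h of life".

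Section 2.8 says that group differences in RDS and surfactant need "will be assessed using the chi-squared test or Fisher's exact test". It also says that "gestational age at birth, matched during enrollment, will additionally be included as a covariate in relevant statistical models". Section 3 names gestational age, sex and perinatal infection as factors in the models. Birthplace and transfer status appear in neither place, nor among the variables listed for collection in section 2.7.

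**The concern.** The groups come from different source populations. Exposed neonates can reach the study by being moved into a level III unit on the first day of life; controls cannot. The article does not say why neonates are transferred, but illness is a plausible reason and respiratory illness a common one. If so, entry by transfer is related to the outcome and is open to one group only.

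Because RDS and surfactant use count from birth to 72 h, the disease that prompted a transfer would itself be an outcome event. NICU admission would be affected in the same way. Early blood samples from a sick, transferred neonate would be compared with samples from inborn controls. The expected direction is upward in the ICP group, which is the direction of the study's hypothesis in section 2.3. Matching on gestational age, birthweight and sex does not remove selection through transfer.

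A second problem lies within the same section. A neonate delivered in another facility would seldom have written study consent at least one hour before birth. Either the transfer route admits almost nobody, or transferred neonates are consented by a process that the article does not describe.

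**Working it through.** **1. The plan's own figure.** Section 2.3 assumes a one-sided t-test, δ = 0.5, α = 0.05 and 66 versus 132. With noncentrality 0.5 × √(66 × 132 / 198) = 3.32 and 196 degrees of freedom, power is 0.9516, which agrees with the stated 0.952. The figure does not depend on birthplace and is not in question.

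**2. Inputs for the bias.** From the article: 66 exposed and 132 unexposed, level 0.05, chi-squared comparison. Assumed, because the article gives no value:
- no true ICP effect;
- RDS risk of 15% in inborn neonates, with 30% as a second case;
- RDS risk of 50–70% in outborn neonates;
- the number of outborn neonates among the 66 exposed.

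The lowest expected event count is 66 × 0.15 = 9.9, so the chi-squared test applies rather than Fisher's.

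**3. Formula.** Let f be the outborn share of the exposed group.

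Exposed risk = (1 − f) × inborn risk + f × outborn risk. The control risk is the inborn risk. Spurious RR = exposed risk / inborn risk.

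Example, 3 of 66 outborn at 70%: (63 × 0.15 + 3 × 0.70) / 66 = 11.55 / 66 = 17.5%, so RR = 17.5 / 15 = 1.17.

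Example, f = 10% at 50%: 0.90 × 0.15 + 0.10 × 0.50 = 18.5%, so RR = 18.5 / 15 = 1.23.

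**4. Results.** Each range runs from outborn risk 50% to 70%. Rejection is the chance that an uncorrected two-sided 5% chi-squared test is significant with no true effect (simulated tables for the 15% case).

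| Outborn among 66 exposed | Inborn 15%: spurious RR | Rejection | Inborn 30%: spurious RR | Rejection |
|---|---|---|---|---|
| 0 | 1.00 | 5% | 1.00 | 5% |
| 1 | 1.04–1.06 | 5% | 1.01–1.02 | 5% |
| 3 | 1.11–1.17 | 6–7% | 1.03–1.06 | 5–6% |
| 10% (about 7) | 1.23–1.37 | 10–17% | 1.07–1.13 | 6–9% |
| 20% (about 13) | 1.47–1.73 | 24–46% | 1.13–1.27 | 9–21% |

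A normal approximation to the same test gives 10–17% and 24–47% for the last two rows of the 15% case, in agreement.

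**5. Biomarkers.** For illustration only, suppose outborn neonates differ by 1 SD. The group means then differ by f × 1 SD: 0.05 SD at a 5% share and 0.10 SD at 10%. The one-sided test of section 2.3 would reject in about 9% and 16% of studies, against a nominal 5%.

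**The case against.** The best defence is that the consent rule already closes the transfer route. Consent must precede birth by at least an hour and is tied to the obstetric team's confirmation of delivery, so few or no outborn neonates could qualify. A bile acid result from the last seven days is also required, and section 3 describes systematic testing only at the study institution. With 1–3 outborn neonates the distortion is barely above nominal even at the assumed rates, and the larger figures need about 13 outborn neonates who each met the consent rule.

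Matching also matters. Controls for a very preterm outborn neonate are equally preterm and have a raised RDS risk of their own. Setting 50–70% against a flat 15% may therefore charge some of the effect of prematurity to transfer. The 30% column shows how much the bias shrinks with a higher baseline.

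These arguments stand as limits on size. They do not defend the clause: if it admits nobody it serves no purpose, and if it admits anyone it does so in one group only.

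A reader might infer that the study is shown to be biased, or that its false-positive rate is as high as 24–46%. The article supports neither. It does not report how many exposed neonates were transferred, why, or how often they had RDS. Only the difference in the rules is explicit; the upward direction is an inference.

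One could also read the controls' birthplace as the hospital where the matched exposed neonate was born. The article does not say this, and the natural reading is the study hospital.

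**Conclusion.** The point holds as a one-sided eligibility rule that no stated matching factor, data item or covariate corrects, together with a transfer clause and a consent rule that must be reconciled. It should be fixed, but it is not shown to invalidate the study.

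The size cannot be known from the article. It is zero with no outborn neonates, close to nominal with 1–3 of 66, and material only from roughly 10% outborn upward, less so if the inborn RDS rate is above 15%. All of these figures rest on the assumed rates and on no true ICP effect.

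**What to change.** Apply one birthplace rule to both groups for further enrolment, with inborn neonates only. Alternatively, keep the transfer route, record birthplace and transfer status for every participant, and restrict the primary comparison to inborn neonates. In either case, describe any transferred exposed neonates already enrolled separately, and reconcile the transfer clause with the consent rule in section 2.4.

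The cost is an amendment to the eligibility text or one added data item, and the loss of a probably small number of exposed neonates from the primary comparison. Any so removed would need replacing to keep 66 in that comparison; the 66 + 132 target itself does not change. The timing is favourable: section 3 reports 54 exposed neonates recruited in 14 months, with control recruitment scheduled to start only after the first year.
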